## Abstract

**Background:**

Malignant pleural effusions (MPEs) remain a common problem, with 40,000 new cases in the United Kingdom each year and up to 250,000 in the United States. Traditional management of MPE usually involves an inpatient stay with placement of a chest drain, followed by the instillation of a pleural sclerosing agent such as talc, which aims to minimise further fluid build-up. Despite a good success rate in studies, this approach can be expensive, time-consuming and inconvenient for patients. More recently, an alternative method has become available in the form of indwelling pleural catheters (IPCs), which can be inserted and managed in an outpatient setting. It is currently unknown whether combining talc pleurodesis with IPCs will provide improved pleural symphysis rates over those of IPCs alone.

**Methods/Design:**

IPC-PLUS is a patient-blind, multicentre randomised controlled trial (RCT) comparing the combination of talc with an IPC to the use of an IPC alone for inducing pleurodesis in MPEs. The primary outcome is successful pleurodesis at five weeks post-randomisation. This study will recruit 154 patients, with an interim analysis for efficacy after 100 patients, and aims to help to define the future gold standard for outpatient management of patients with symptomatic MPEs.

**Discussion:**

IPC-PLUS is the first RCT to examine the practicality and utility of talc administered via an IPC. The study remains in active recruitment and has the potential to significantly alter how patients requiring pleurodesis for MPE are approached in the future.

**Trial registration:**

This trial was registered with Current Controlled Trials (identifier: ISRCTN73255764) on 23 August 2012.

## Background

Malignant pleural effusions (MPEs) are a common complication of many cancers, with 40,000 new cases in the United Kingdom each year and up to 250,000 in the United States [1]. Their presence usually indicates metastatic disease, and hence possibly a poorer prognosis.

The traditional management of MPE involves inpatient insertion of a chest drain, to ensure fluid drainage and pleural apposition, before the instillation of a sclerosant substance to cause pleural inflammation and adhesion, also known as pleurodesis. Many substances can be used as a pleural irritant, although by far the most commonly used worldwide is talc, which has been shown to be superior to numerous alternatives [2].

Quoted pleurodesis success rates are typically high with talc, ranging from 81 to 100% [3], although these figures may vary considerably in real-world practice due to differences between clinicians and between the practices of individual centres. To achieve such high efficacy, a patient typically requires admission for the insertion of a chest tube and drainage. Only once the pleural space is felt to be dry is the talc inserted. This usually requires an inpatient stay of five to seven days [4,5], which can have a significant health economic impact, as well as the potential to impair the quality of remaining life for patients. Following the widespread use of large-particle talc, the side effects of pleurodesis have tended to be minor, the commonest of which are fever, pain and gastrointestinal upset [2,6,7], although there have been rare cases of empyema [8].

The main drawback of the traditional method of pleurodesis is the length of hospital stay and the inconvenience to patients. In more recent years, indwelling pleural catheters (IPCs) have become more widely used and may the potential to alleviate these problems.

IPCs are silastic tubes, which have the potential to be left in place for weeks to months after being tunnelled under the skin. They can be inserted under local anaesthetic or at thoracoscopy, and are usually performed as a day case. Once at home, the aim is to drain fluid regularly (usually three times per week) in the patient’s own environment. This maximises the opportunity for pleural apposition and adhesion, which potentially leads to complete pleurodesis. Drainage can be performed by anyone with appropriate training, including the patient, but is often managed by district nursing teams.

IPCs have been shown to be effective in the management of MPEs, although there is a paucity of evidence comparing them directly to talc pleurodesis. In a retrospective series of 250 cases, almost 90% of patients experienced complete or partial relief of dyspnoea [9], a finding bettered in a later study in which all patients experienced improvement [10]. Indwelling drains have also been shown to improve other outcomes, such as length of hospital stay and future admissions, even in comparison to talc pleurodesis [4,11]. Despite the need for proprietary drainage kits, they may also be cheaper overall to healthcare providers, if used for limited periods of time [12].

Regardless of patients’ short life expectancies, this is an achievable goal as IPCs can often be removed following sustained reduction in drainable fluid volumes, a reliable surrogate indicator for pleurodesis. Such spontaneous pleurodesis generally occurs in around 50% of cases [4,10,13] and is heavily influenced by the underlying tumour type [14], although rates as high as 70% were reported in one study [15]. The presence of ‘trapped lung’ (usually due to central airways obstruction or visceral pleural fibrosis) can lead to incomplete expansion following pleural fluid drainage, which no doubt influenced the variability of the time to pleurodesis in these studies. Indeed, in patients with trapped lung, the persistent failure of pleural apposition makes the achievement of any degree of pleurodesis much less likely overall, meaning regular fluid management with an IPC may be the only feasible approach to their care.

However, IPCs are not without drawbacks. There may be significant pain associated with the immediate and short-term post-procedure period, and in some cases pleural tract metastases have been documented [16]. Complications including empyema formation (3%), secondary fluid loculation (12%) and cellulitis (2%) have also been reported [9]. Nevertheless, meta-analysis data has shown IPCs are generally safe to use, with an overall complication rate of 12.5%.

It would seem, therefore, that the optimal approach to the management of MPEs should be the combination of talc instillation, to achieve the highest pleurodesis rates and long-term fluid prevention, and placement of an IPC to allow greater convenience and quality of life for the patient. This should also theoretically lead to reduced overall healthcare costs when compared to either individual method. Despite the potential for combining fluid management approached being recognised in the literature, [17] there have been no studies to date to test this hypothesis, although ambulatory pleurodesis for malignant effusions was attempted in one small series by Saffran *et al*. [18]. In this study, a closed-system pigtail catheter was inserted and pleurodesis was attempted at a later date using four grams of talc. Patients were managed as outpatients and the authors describe their method as being a viable alternative to traditional inpatient management. However, patient numbers were limited to 10 and there was no attempt at randomisation. The study took place before the widespread introduction of IPCs.

The IPC-PLUS trial aims to test the hypothesis that the combination of talc in addition to IPCs is superior to IPCs alone in the management of MPEs. This trial has the potential to significantly affect, on a global scale, the way in which such effusions are managed in the future.

## Methods/Design

### Study questions

Our primary research question is, ‘In patients with a proven MPE, does the use of talc as a sclerosant in conjunction with an IPC increase the number of patients achieving successful pleurodesis, when compared to using an IPC alone?’

Our secondary research questions are as follows:Does using talc and an IPC together alter the amount of pain and breathlessness a patient experiences, when compared to using an IPC alone?Does the use of talc and an IPC together alter a patient’s quality of life, when compared to using an IPC alone?What are the medical complications of using talc in conjunction with an IPC?What are the logistical and clinical difficulties with using talc in conjunction with an IPC?Does the combination of talc and an IPC together influence the degree of fluid septation and loculation seen on thoracic ultrasound?Does the baseline level of serum brain natriuretic peptide (BNP) correlate with the volume of pleural fluid drained and chance of successful pleurodesis?Does pleural elastance during initial drainage correlate with lung entrapment and the chance of successful pleurodesis?Is using talc in combination with IPC cost-effective when compared to IPC alone?

### Sample size and power calculation

Talc pleurodesis alone has been shown to be up to 90% efficacious in trial conditions [3], and we expect the combination of talc and IPC to be at least as effective as talc alone. IPCs used alone have a more variable range for pleurodesis efficacy, but suggest an average rate of around 50%.

Therefore, in order to detect a 25% difference in pleurodesis success at five weeks (using conservative estimates of 60% IPC alone versus 85% IPC and talc) with 90% power, a 5% significance level and 5% loss to follow-up, we would require 154 patients (77 in each arm). An interim analysis for efficacy will take place after 100 patients are randomised.

### Ethics, approvals and sponsorship

The study is sponsored in the United Kingdom by North Bristol NHS Trust, and has been granted the necessary (national) approvals by both the Oxford A Research Ethics Committee (approval number: 12/SC/0242) and the Medicines and Healthcare Products Regulatory Agency (MHRA) (EudraCT number: 2012-000599-40).

### Investigational product: Novatech Steritalc®

Medicinal sterile talc as used in this trial is mined in Luzenac, France. It is marketed in the United Kingdom as Steritalc® and imported by GB UK Healthcare Ltd (Selby, UK). Talc is a naturally occurring mineral which, when processed for medical use as Steritalc, takes the form of a white powder of controlled particle size (graded). It is not licensed in the United Kingdom but is commonly used for the induction of pleurodesis, usually to prevent recurrence of MPEs or pneumothoraces. Medicinal talc has been licensed by the Food and Drug Administration (FDA) in the United States since 2003. Prior to introduction into the pleural cavity it is reconstituted into slurry using an inert solvent such as 0.9% saline. The typical dose of talc is two to four grams. Common side effects following pleural administration of talc are mild pleuritic pain and low-grade fever.

### Study setting and design

The IPC-PLUS study is a non-commercial, patient-blind, multicentre, randomised controlled trial of a medicinal product. Patients will be recruited from multiple centres within the United Kingdom. The trial is supported by the appropriate local and regional cancer networks.

Clinical care, drain insertion and imaging will be provided by local medical professionals at the patients’ base hospitals or appropriate satellite centres. Further care will be provided by ward and specialist nurses in these centres, who will also be available for telephone support. Routine drainage of pleural fluid will take place in the community and at follow-up visits. All drainages up to the 28-day post-randomisation visit will be performed by appropriately trained medical staff such as district nurses, lung cancer specialist nurses or research nurses. After this, drainages may be performed by anyone who has been appropriately trained (except the patient themselves).

### Patient population

Trial patients will be recruited from those presenting with symptomatic MPEs. As part of their normal clinical care, it will have been decided that outpatient treatment with an IPC is the most appropriate strategy for fluid management.

### Inclusion criteria

The inclusion criteria for this trial are as follows:Symptomatic MPE, agreed at appropriate local or regional level to require an IPC, defined as pleural fluid in the context of one of the following: a histocytologically proven pleural malignancy; an otherwise unexplained pleural effusion in the context of clinically proven cancer elsewhere or a radiologically proven pleural malignancy, as diagnosed in normal clinical practice on thoracic CT, in the absence of histocytological proof.Expected survival of more than two months and the Eastern Co-operative Oncology Group/World Health Organisation (ECOG/WHO) performance status of two or more. Patients with a performance status of three may be included if it is felt that removal of the pleural fluid would improve their performance status to two or better.Written informed consent to trial participation.

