SA06	• New sites added: Northampton, Ayr, Cambridge, Aintree and Hull
	• Change of inclusion criteria to require World Health Organisation (WHO) performance of two or better to be eligible, three if score will decrease to two after drainage.
	• Allow patients with previous pleurodesis as long as longer than 56 days before trial entry
	• Relax follow-up visits by allowing day 42 and 56 to be carried out over the telephone
	• Allow carers or relatives to perform chest drains after the day 28 post-randomisation visit
	• Extend recruitment period to May 2015
	• Relaxation of manometry recordings from every 100 ml to every 100 to 200 ml
	• Updated membership of the Trial Steering Committee

The following CRFs will be used during the trial: enrolment, baseline assessment, IPC insertion, day 10 assessment and randomisation, follow-up, telephone follow-up, thoracic ultrasound appearances, health resource utilisation and withdrawal.

In addition to the above, patient data will also be collected via a daily patient VAS score booklet and a daily IPC drainage volume booklet.

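### The performance-status inclusion limit is worded in the wrong direction and conflicts with the sentence that follows it

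*Protocol article*

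**What the plan says.** The second inclusion criterion in the protocol article (Inclusion criteria) joins an expected survival of more than two months to an "ECOG/WHO) performance status of two or more". The sentence directly after it reads "Patients with a performance status of three may be included if it is felt that removal of the pleural fluid would improve", and the stated condition is that drainage "would improve their performance status to two or better".

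Table 2 (List of major protocol amendments) describes the same criterion under SA06, the last amendment listed. There the requirement is WHO "performance of two or better to be eligible, three if score will decrease to two after drainage".

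The section Screening and consent says that patients are screened against these criteria, so the sentence is meant as a rule and not as background.

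**The concern.** On the ECOG/WHO scale a lower score means better function. The article shows this itself: moving from three to two is called an improvement, and SA06 speaks of the score decreasing. A requirement of two *or more* therefore sets a floor on disability, where the following sentence presupposes a ceiling.

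What is at stake is the stated trial population. Performance status is one of the few items that tell a reader to whom the result applies. It also bears on prognosis, and prognosis matters here: under Primary endpoint, patients who die within the 10 weeks are judged on pleurodesis achieved before death, and under Statistical analysis plan, mortality is a competing risk in the primary model. The rule that fixes how frail the entrants may be should therefore be readable in only one way.

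**Working it through.** No arithmetic applies. The check sets the sentences side by side.

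**Inputs**
- First sentence of the criterion: "ECOG/WHO) performance status of two or more".
- Second sentence: "Patients with a performance status of three may be included if it is felt" that fluid removal "would improve their performance status to two or better".
- SA06 in Table 2: "performance of two or better to be eligible, three if score will decrease to two after drainage".
- Assumption: the standard scale, with living patients graded 0 to 4. The article does not print the range. The direction of the scale does not depend on this assumption, because the second sentence fixes it.

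**Step 1. Direction of the scale.** The second sentence calls a move from three to two an improvement. So three is worse than two, and lower is better.

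**Step 2. Who qualifies under each reading.**

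| Status | First sentence taken alone | Limit implied by the second sentence and stated in SA06 |
|---|---|---|
| 0 | no | yes |
| 1 | no | yes |
| 2 | yes | yes |
| 3 | yes | only under the condition |
| 4 | yes | no |

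The two readings agree without condition on status 2 alone.

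**Step 3. Can both sentences stand?** If the first is taken literally, status three is already eligible and the conditional sentence is redundant. If the conditional sentence has any effect, status three lies outside the main rule, so the main rule is an upper limit of two. Both cannot hold as written, and the conflict is complete within this one criterion.

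**Step 4. Does the article reflect the protocol after SA06?** Other changes listed under SA06 appear in the current text:
- the 56-day rule on previous pleurodesis (Exclusion criteria);
- optional telephone visits on days 42 and 56 (Clinical assessments);
- drainage by family or carers after the day 28 visit (Community drainage);
- manometry every 100 to 200 mls (Pre-randomisation).

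The article thus presents the amended protocol. SA06 says what the criterion was changed to, and nothing visible supports two or more.

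**The case against.** The strongest reply is that the text largely corrects itself. Anyone who reads the whole criterion sees that status three is conditional and that lower is better. Once three is conditional, admitting four freely is not a coherent reading. This stands, and it is why the point is a wording error and not evidence of a wrong design.

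A reader might go further and infer that the trial recruits the patients least likely to live to the endpoint and that its results will describe the wrong population. The documents do not support that:
- The same criterion also requires an expected survival of more than two months, which limits any excess of early deaths even under the literal reading.
- Patient population adds that outpatient treatment with an IPC must already have been judged the most appropriate strategy.
- No passage shows that a site applied the reversed wording, or that anyone was wrongly enrolled or refused.
- The article condenses a full protocol that is not shown. The slip may exist only in the article.

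A reader might also count SA06 as a second contradiction. It is not one: a difference between an amendment log and the current text is not in itself an error. SA06 serves here only to corroborate the intended wording, and the finding holds without it.

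What does not fall away is that a core eligibility rule, stated in full, points the wrong way. Condensing a protocol may drop detail, but it does not explain a reversed limit.

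**Conclusion.** The point holds as an error of wording in an eligibility rule. The first sentence sets the limit in the wrong direction. Taken literally, it excludes status 0 and 1 and leaves the exception for status three with no function. The most likely explanation is *more* written for *better*.

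Its size is limited. The share of patients who would be classified differently cannot be given, because the article reports no distribution of performance status. No effect on recruitment is shown. The target of 154 patients, the significance level and the analysis model do not depend on this sentence.

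The conclusion rests on the criterion's own two sentences. Naming status 0, 1 and 4 also assumes the standard scale. Figure 1, whose legend lists performance status, is not shown and could not be checked.

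**What to change.** Reconcile the first sentence with the one that follows it and with SA06, so that the main limit and the exception for status three point the same way. Confirm that the trial flow chart and the eligibility case report form carry the same direction.

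If entered patients are checked, hold each one to the version of the criterion in force at entry. SA06 is listed as a change of the inclusion criteria and was made during the trial. Applying its wording to everyone randomised could therefore label earlier entrants as violations of a rule that did not yet exist. The check is feasible, because current performance status is recorded at the baseline assessment (Pre-randomisation).

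The cost is a one-word correction and a look at two trial documents. According to Trial status, 60 of the planned 154 patients had been randomised by July 2014 and three further sites were in set-up, so a clear wording would still serve most of the recruitment.

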### Exclusion criteria

The exclusion criteria for this trial are as follows:Aged under 18 years.Females who are pregnant or lactating.Patient is unable to provide informed consent.Previous attempts at pleurodesis have been made within the last 56 days on the same side as the effusion requiring management.Previously documented adverse reaction to talc or lidocaine.Community services are unable to drain the IPC at least twice per week.Evidence of extensive lung entrapment on a chest X-ray or computed tomography (CT) scan, or significant fluid loculation on an ultrasound scan, to a level which would normally be a contraindication to attempted talc pleurodesis or IPC insertion.Other contraindication to IPC insertion.Patient has no access to a telephone.

### Screening and consent

Patients will be screened using the inclusion and exclusion criteria as described above. Screening logs documenting reasons for exclusions will be kept throughout the trial. Those who may be suitable for an IPC will have this option discussed in a normal outpatient or inpatient setting, where they will also be given the option of participating in the IPC-PLUS trial. Eligible patients will be invited to participate on a consecutive basis, and will be provided with an information leaflet at the earliest opportunity. They will be allowed sufficient time, as determined by the patient, to fully consider trial entry, as well as to ask questions of investigators. Written informed consent to trial participation will be obtained prior to enrolment. Consent must be taken by a member of the trial team and should take place before the placement of the patient’s IPC.

### Trial interventions

The trial interventions are summarised in Table 1 and in Figure 1 (trial flow chart).

**Table 1 Tab1:** **Visit schedule**

	**Timings**										
**Event**	**Pre-screening**	**Consent/baseline**	**IPC insertion**	**Pre-randomisation**	**Randomisation**	**Follow-ups (days post-randomisation)**					**On-going**
						**14**	**28**	**42** ^**a**^	**56** ^**a**^	**70**	
Provide patient information sheet	X										
Sign consent		X									
Thoracic ultrasound		X			X	X	X	X	X	X	
Chest X-ray			X		X	X	X	X	X	X	
Standard blood tests		X									
Trial blood samples (Southmead and Oxford only)		X									
Trial pleural fluid samples (Southmead and Oxford only)			X		X	X	X	X	X	X	
Manometry			X								
Instillation of talc/placebo					X						
Community IPC drainages				X^b^							X
Drainage booklet			X								X
Daily VAS scores				X	X						X
Collection of VAS booklet					X	X	X	X	X	X	
EQ-5D questionnaire		X			X	X	X	X	X	X	
QLQ-C30 questionnaire		X			X	X	X	X	X	X	
Patient diary				X							X

IPC = Indwelling pleural catheter.

VAS = Visual analogue scale.

EQ-5D = EuroQuol 5D.

QLQ-C30 = Quality of Life Questionnaire C30.

^a^Visits at days 42 and 56 may be done over the telephone and therefore the patient would not have a chest X-ray or thoracic ultrasound.

^b^Minimum of three drainages in the community between IPC insertion and randomisation.

